## Abstract

**Background:**

A majority of stroke survivors present with cognitive impairments. Attention disturbance, which leads to impaired concentration and overall reduced cognitive functions, is strongly associated with stroke. The clinical efficacy of acupuncture with Baihui (GV20) and Shenting (GV24) as well as computer-assisted cognitive training in stroke and post-stroke cognitive impairment have both been demonstrated in previous studies. To date, no systematic comparison of these exists and the potential beneficial effects of a combined application are yet to be examined. The main objective of this pilot study is to evaluate the effects of computer-assisted cognitive training compared to acupuncture on the outcomes of attention assessments. The second objective is to test the effects of a combined cognitive intervention that incorporates computer-assisted cognitive training and acupuncture (ACoTrain).

**Methods/Design:**

An international multicentre, single-blinded, randomised controlled pilot trial will be conducted. In a 1:1:1 ratio, 60 inpatients with post-stroke cognitive dysfunction will be randomly allocated into either the acupuncture group, the computer-assisted cognitive training group, or the ACoTrain group in addition to their individual rehabilitation programme. The intervention period of this pilot trial will last 4 weeks (30 minutes per day, 5 days per week, Monday to Friday). The primary outcome is the test battery for attentional performance. The secondary outcomes include the Trail Making Test, Test des Deux Barrages, National Institute of Health Stroke Scale, and Modified Barthel Index for assessment of daily life competence, and the EuroQol Questionnaire for health-related quality of life.

**Discussion:**

This trial mainly focuses on evaluating the effects of computer-assisted cognitive training compared to acupuncture on the outcomes of attention assessments. The results of this pilot trial are expected to provide new insights on how Eastern and Western medicine can complement one another and improve the treatment of cognitive impairments in early stroke rehabilitation. Including patients with different cultural backgrounds allows a more generalisable interpretation of the results but also poses risks of performance bias. Using standardised and well-described assessments, validated for each region, is pivotal to allow pooling of the data.

**Trial registration:**

Clinical Trails.gov ID: NCT02324959 (8 December 2014)

## Background

Cognitive impairment is a condition characterised by mental deficits. Cognitive deficits occur in more than half of stroke survivors and are deemed to be more important determinants of health- and quality of life-related outcomes than physical disability [1, 2]. The most common type of cognitive deficit is impaired attention, with a point prevalence between 46 % and 92 % reported in acute stroke survivors [3]. These deficits along with difficulties to concentrate and continued decline in cognitive functions severely affect quality of life [4–7].

Attention is closely related to and involved in most cognitive functions, such as most processes of perception, memory [8], planning and acting [8], speech perception [9], spatial orienting [10], and social problem-solving [11]. Accordingly, attention can be considered a basic competence necessary for most practical and intellectual performances [12]. Consequently, it cannot be isolated, whether conceptually or functionally, from other cognitive functions. It has further been shown that these deficits impair certain motor abilities and inhibit motor learning [13]. Impairments of attention are a major problem for people with stroke and affect rehabilitation outcome [14]. A systematic review on cognitive training for post-stroke attention deficits, which included six randomised controlled trials (RCTs) with 223 participants [14], suggested that there may be a short-term effect on attention abilities. However, due to the methodological limitations of the reported studies, there was insufficient evidence to support or refute the persisting effects of cognitive rehabilitation on attention or on functional outcomes.

Acupuncture is one of the main modalities of treatment in Traditional Chinese Medicine (TCM) and has a practical history of more than 2000 years in China [15]. A recent meta-analysis [16] was conducted to evaluate the efficacy of acupuncture on cognitive impairment (function) after stroke. Twenty-one trials with a total of 1421 patients were included. The cumulative findings suggest that acupuncture has positive effects on cognitive function after stroke. According to TCM theory of acupuncture, the Du meridian plays an important role in treating attention problems [17]. Baihui (GV20) and Shenting (GV24) are two main acupoints from the Du meridian which are believed to activate the spirit. Previous studies with experimentally induced cerebral ischemia injuries in rodents [18, 19] showed improved learning and memory abilities after 4 weeks (five times per week, 30 minutes per time) of Baihui (GV20) and Shenting (GV24) acupuncture treatment. However, the existing literature of the effects of acupuncture on cognitive impairment after stroke describes general cognitive functions and do not provide sufficient evidence as to how acupuncture could improve attention deficits after stroke.

The aims of our study are: (1) to observe the effect of acupuncture combined with RehaCom training on cognitive dysfunction (in particular attention disturbances) after stroke, and (2) to test efficacy compared to conventional treatment combined with acupuncture or conventional treatment combined with RehaCom training.

## Methods

### Study design and setting

The study is designed as an international multicentre study with randomised, controlled group comparators and blinded assessors. The study will be an explorative pilot study with three parallel treatment groups: computer-assisted cognitive training (CaCT), acupuncture (AP), and intervention that incorporates CaCT and AP (ACoTrain, ACT). Three neurological rehabilitation clinics from three different countries will be involved in recruitment, treatments and assessments. Each clinic will aim to recruit 20 inpatients currently recovering from their clinically first-ever stroke. Attention performance will be assessed as the primary study outcome in all groups before and after a 4-week intervention. The multicentric body of trial centres consists of specialised neurological rehabilitation centres from China (Fujian University of Traditional Chinese Medicine, A), Switzerland (Reha Rheinfelden, B), and Germany (m&i Fachklinik Herzogenaurach, C). Fig. 1 illustrates the flow chart of patient allocation and study design.

**Fig. 1 Fig1:**
[figure not shown]
Flow diagram of study design including the process of recruitment, allocation and intervention, and assessment

### Sample size

The international setting is thought to increase the generalisability of the study results, as the study sample will include patients with different cultural background. However, it is also expected that high heterogeneity regarding affected cortical areas and functional ability within the study groups of stroke patients will occur. The number of participants will therefore not suffice to conduct a full-scale study but are thought to provide a basis for estimation of the effects and planning of a larger follow-up study, if proven feasible.

The aim is to recruit 20 patients per clinic (N_total_ = 60). The results will be used to compute sample size and conduct a power calculation to plan the full-scale follow-up study.

### Participant and recruitment

The participants will be recruited from three inpatient stroke rehabilitation units from (1) Fujian University of Traditional Chinese Medicine Subsidiary Rehabilitation Hospital; (2) m&i-Fachklinik Herzogenaurach; and (3) Reha Rheinfelden. Patients will be identified and recruited via the clinic’s database according to diagnosis and medical referral. Respective medical personnel will be asked to invite patients from the population under investigation. Patients who express a general interest in taking part in the study will meet with one of the study personnel to receive all necessary information in oral and written form. After a 24-hour consideration period, the patient will be reapproached by the investigator to resolve any uncertainties and to be invited to sign informed consent after an assessment of eligibility criteria. After baseline assessment, patients who meet the inclusion criteria will be randomly allocated to one of the three study groups. A CONSORT diagram of participant recruitment is shown in Table 1.

**Table 1 Tab1:** Trial processes chart

Study periods	Admission	1^st^ *c*ontact	2^nd^ *c*ontact	Eligibility	Assessment	Treatment	Follow-up
Visit Duration	Week 1	Week 1	Week 1	Week 1	Week 1	Week 2–5	Week 6
		10 min	10 min	1 hour	3 hours	(4 × 5 × 30 min)	3 hours
Time	−7d	−6d	−5d	−4d	−4-0d	−2d	27d
Admission	x						
Medical examination	x						
Patient information		x			x		
Consultation			x				
Informed consent				x			
Demographics				x			
Medical history				x			
In-/exclusion Criteria				x			
Randomisation						x	
Administer study						x	
Primary variables					x		x
Secondary variables					x		x
Concomitant therapy						x	
Adverse events						x	x

### Inclusion criteria

In order to properly understand and apply the training methods and the content of the study, the patients are required to have some level of cognition. To assess the minimum level required, the Montreal Cognitive Assessment (MoCA) [20] will be applied at baseline (BL). Patients eligible for the trial must comply with all of the following criteria prior to randomisation: (1) clinically first-ever stroke, diagnosis confirmed by CT or MRI; (2) aged between 18 and 80 years old; (3) clinically confirmed attention deficits (>1SD below mean of age-matched norm in at least one subtest of the Test for Attentional Performance, TAP); (4) inclusion within 6 months after stroke onset; (5) conscious, stable physical condition; and (6) given oral and written consent confirmed by the signature of the patient.

### Exclusion criteria

Patients who are positive to one or more of the following criteria will have to be excluded: (1) self-reported severe visual problems (inability to recognise illustrations on MoCA); (2) hearing problems (TAP discrimination of tones >1SD of aged-matched norm); (3) notable deficiencies in MoCA submodalities on visuospatial and attention assessments, neglect or hemianopia <2 points on visuospatial assessments, failed attention test (read list of letters and tap on every *A*), inability to concentrate throughout the MoCA assessment, inability to execute a standardised three-step instruction: “*Please take this piece of paper, fold it twice to fit it in this standardized envelope and hand it back to me*.”; (5) speech comprehension deficits: <9 points on the short aphasia test (KAP); (6) seizures; (7) pre-existing psychological disorders prior to stroke; (8) severe medical condition (e.g. critical diabetes with hyper- or hypoglycemia); (9) pregnancy (in doubt, a pregnancy test will be required); (10) self-reported, family-reported or neuropsychological assessment proves cognitive decline in history before the onset of stroke.

### Randomization and blinding

For the randomisation, restricted randomisation with random block sizes between 3 and 9 (exact size to be determined by an external institution) will be used. This will reduce opportunities for bias and confounding and increases the probability to meet the assumptions of statistical analysis (treatment groups are random samples of population) [21]. Each centre will receive a computer-generated randomisation list (MATLAB 2007b, Mathworks Inc., Natick, MA, USA) from a third-party partner institution, which is elsewise not involved in the study. Sequentially numbered opaque and sealed envelopes will be distributed to each trial centre by a third-party employer, who is not part of the investigating team. The treating therapist will inform the participants after baseline assessment immediately before the first treatment. The assessor remains uninformed about group allocation. Patients will be informed and reminded not to mention the study treatment in front of the assessors.

### Ethical issues

This study will be conducted in compliance with study protocol and the current version of the Declaration of Helsinki. All participants will be fully informed about the trial, and will sign the written informed consent form prior to participation. The trial has been approved by the ethics committee of the Rehabilitation Hospital affiliated to Fujian University of Traditional Chinese Medicine (Approval No. 2013KY-004-02); the local committee responsible for Germany – the Medical Faculty of the Friedrich-Alexander University in Erlangen-Nürnberg (Approval No. 119_14Mz); and the local ethics committee responsible for Northwestern and Central Switzerland (Ethikkommission Nordwest und Zentralschweiz EKNZ) (Approval No. EKNZ 2014–106).

### Interventions

All study interventions are described in Table 2 using the Template for Intervention Description and Replication checklist and guide, known as TIDieR. Patients will be evenly allocated to CaCT, AP, or ACT. All groups will additionally receive conventional neurorehabilitative treatment as prescribed by each clinic. The experimental intervention of this trial will be added to the existing therapy plan as a daily treatment of 30 minutes for 4 weeks (Monday to Friday). Every treatment will be documented on the therapy documentation sheet (standardised for each trial centre).

**Table 2 Tab2:** Description of study interventions based on the TIDieR template^*a^

Item	Computer-assisted cognitive training	Acupuncture	ACoTrain
1 Short name	Ca CT	AP	ACT
2 Why	Main objective is to evaluate the effects of computer-assisted cognitive training CaCT compared to AP on the outcomes of attention assessments		
	Second objective is to test the effects of a combined cognitive intervention that incorporates CaCT and AP		
3 What: materials	Ca CT (RehaCom, Hasomed Inc., Germany, http://www.hasomed.de) will be conducted in the study. Patients will sit in front of the RehaCom system. The training program will be displayed on the computer screen and they also can hear the sound feedback from the audio system. According to different training programs, patients will press a special RehaCom keyboard with large buttons to react	Acupuncture needle, which is single use, φ 0.35 × 40 mm, will be used for acupuncture treatment. The angle of insertion is approximately 10°–20° (between needle and scalp), the needle should be inserted to a depth of approximately 0.3–0.5B-cun	For the combined group, patients will receive AP and CaCT combined, i.e. the CaCT will be performed while the needles are inserted
4 What: procedures	For the purpose of this study, three submodalities of attention will be targeted with CaCT: intensity, selectivity, and divided attention [26]. To approach intensity of attention, the RehaCom modules “Attention and Concentration (AUFM)” and “Vigilance (VIGI)” will be used. For selectivity, the RehaCom task called “Alertness” for reaction behaviour and reactivity will be used. Divided attention will use the task called “Divided Attention Training 1 and 2”. Each task will start at the lowest difficulty level to allow progression according to the patient’s abilities. Only “Attention and Concentration” and “Divided Attention Training 2” will begin with level 4 and 2 respectively. A detailed description of the tasks and their content can be found on the developer’s site (Hasomed GmbH, www.hasomed.de)	The treatment will be performed after sterilisation of the skin on the areas where the needles will be inserted. The patient will be instructed to lie supine or to sit down on a treatment chair while the doctor’s left hand fixates the target position (DU20 and DU24), The angle of insertion is approximately 10°–20°(between needle and scalp), the needle should be inserted to a depth of approximately 0.3–0.5B-cun. Following insertion, a 1-minute stimulation of the acupuncture point will be performed using bidirectional rotation of the needle’s sleeve. This provokes a sensation known as Deqi, which is commonly described as a ‘glowing’ feeling. The needle will be kept in this position for 30 minutes. The described manipulation will be repeated every 10 minutes and the needles will be withdrawn after the fourth manipulation	
5 Who provides	RehaCom training will be provided by experienced neuropsychology therapists, who will have at least 2 years of professional experience in the field of neurorehabilitation.	Acupuncture will be performed by acupuncturists who have a TCM practitioner’s license, and at least 2 years of working experience	Both study interventions will be provided by experienced neuropsychology therapists and acupuncture therapists, who will have at least 2 years of professional experience
6 How	All the study interventions will be conducted individually in one-to-one sessions		
7 Where	All the study interventions will take place in the neuropsychology therapy department of each participating centre		
8 When and how much	During the 4-week intervention program, patients in each study group will receive the same amount of 20 sessions lasting 30 minutes each		
9 Tailoring	Training and therapy content will be tailored to each patient’s preferences, and the concentration level of each patient		

^*^
*Ca CT* computer-assisted cognitive training, *AP* acupuncture, *ACT* AcoTrain, *TCM* Traditional Chinese Medicine

^a^Items 10, 11 and 12 of the Template for Intervention Description and Replication checklist and guide (TIDieR) template do not apply to this study

### Conventional therapy

All participants will receive basic treatment according to the rehabilitation concept applied in the individual clinics and/or as demanded by cost bearers. Multidisciplinary treatment will include physiotherapy, occupational therapy, medical exercise therapy, hydrotherapy, etc. Patients will not be restrained from CaCT or AP training if this is part of the conventional therapy of the individual clinic. However, each trial centre is instructed to track the types of interventions provided and provide precise documentation of therapy treatments, medication, therapy frequency and dose.

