### Computer-assisted cognitive training with RehaCom

It is important to note that the CaCT group will use RehaCom (Hasomed Inc., Magdeburg, Germany, http://www.hasomed.de) in our study. Three rehabilitation centres from different countries will be involved in our study. Traditional cognitive training programs are delivered in individual or group format by a trained instructor, and differ primarily with regards to trained abilities, length and frequency of training, and specific strategies practiced [22]. Therefore, it is better to use a computer-assisted training program to ensure patients from different centres will all receive equal treatments. RehaCom has been translated into different languages and extensively used in cognitive rehabilitation following the relevant diseases, for example, stroke [23], schizophrenia and multiple sclerosis [24, 25].

The software has five different therapeutic programs aimed at restoration of attention, memory, executive functions, or visual field. Each program has one to four different tasks to choose from for each therapy session.

For the purpose of this study, three submodalities of attention will be targeted with CaCT: intensity, selectivity, and divided attention [26]. To approach intensity of attention, the RehaCom task called “Attention and Concentration” and “Vigilance” will be used. For selectivity the RehaCom task called “Alertness” for reaction behaviour and reactivity will be used. Divided attention will use the task called “Divided Attention Training 1 and 2”. Each task will start at the lowest difficulty level to allow progression according to the patient’s abilities. Only “Attention and Concentration” and “Divided Attention Training 2” will begin with level 4 and 2 respectively. A detailed description of the tasks and their content can be found on the developer’s site (Hasomed GmbH, www.hasomed.de).

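### Usual care may include CaCT or AP in any arm without a stated cap; the named analysis uses neither centre nor the usual-care log, so adding both is a cheap, optional aid to interpretation

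*Protocol article*

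**What the plan says.** The trial adds one of three study treatments to ordinary rehabilitation. The abstract says patients receive it "in addition to their individual rehabilitation programme", and the aims in the Background describe the comparators as "conventional treatment combined with acupuncture or conventional treatment combined with RehaCom training". The add-on design is therefore openly stated.

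The Conventional therapy section leaves usual care to the clinic or the cost bearer, and then states: "Patients will not be restrained from CaCT or AP training if this is part of the conventional therapy of the individual clinic". No limit on amount is given. The next sentence is a safeguard: "each trial centre is instructed to track the types of interventions provided and provide precise documentation of therapy treatments, medication, therapy frequency and dose". The trial processes chart (Table 1) also lists concomitant therapy during the treatment period.

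On structure, "Each clinic will aim to recruit 20 inpatients", there are three clinics, and allocation is 1:1:1. Under Randomization and blinding, "Each centre will receive a computer-generated randomisation list". Under Statistical methods, outcomes are compared by ANOVA or, if not normal, by Kruskal-Wallis. Post hoc work on significant interactions involving group is mentioned, but the second factor is not named. Neither centre nor the usual-care log appears there.

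The Discussion concedes that effects of conventional and experimental treatment are hard to separate. It answers that the aim is to compare the three experimental interventions with each other.

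**The concern.** CaCT and AP are the two components that define the arms. If a clinic gives AP as part of its ordinary programme, its CaCT patients receive CaCT plus some AP, which moves them towards ACT. Its CaCT-versus-AP contrast then becomes CaCT plus AP against a larger dose of AP. A clinic that gives CaCT does the reverse. Both objectives are touched: the main one (CaCT versus AP) and the second one (the combination).

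The limitation in the Discussion concerns conventional against experimental effects. It does not mention that conventional therapy may itself contain an experimental component.

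What is at stake is interpretation. A small ACT advantage could mean that the combination adds little, or that usual care already supplied part of it. One pooled CaCT-versus-AP figure could average different comparisons. Centre is where such a difference would show, and the analysis as named does not look there.

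**Working it through.** **Inputs from the protocol.** Three clinics of 20 give 3 × 20 = 60, which matches the stated total. At 1:1:1 that is 60/3 = 20 per arm, and within one clinic 20/3 ≈ 6.7 per arm. The study dose is 20 × 30 = 600 minutes in each arm. The Sample size section gives no effect size, SD or power, so there is no power figure to reproduce.

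**Assumed inputs (the protocol gives none).**
- k: the number of the three equal-sized clinics that give the missing component to all their patients as usual care.
- e: the redundancy between usual-care and study delivery of that component. At e = 0 the effects add fully. At e = 1 the 600 study minutes add nothing, which is an extreme.

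**1. ACT versus a single arm.** In an exposed clinic the contrast keeps a share 1 − e; elsewhere it is intact. Averaged over three clinics, the factor is 1 − (k/3)e.

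| k | e = 0 | e = 0.5 | e = 1 |
|---|---|---|---|
| 0 | 1.00 | 1.00 | 1.00 |
| 1 | 1.00 | 0.83 | 0.67 |
| 2 | 1.00 | 0.67 | 0.33 |

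**2. CaCT versus AP.** Assume each is worth c = a = 0.4 SD, so the true difference is zero.
- AP clinic: c − a(1 − e) = 0, 0.2, 0.4 SD for e = 0, 0.5, 1.
- CaCT clinic: c(1 − e) − a = 0, −0.2, −0.4 SD.
- One AP clinic of three, pooled: 0, 0.067, 0.133 SD.
- One AP clinic and one CaCT clinic: the pooled shift is 0, while those two centres differ by 0, 0.4, 0.8 SD.

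These figures scale in proportion to the assumed 0.4 SD.

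**3. The pilot's own precision.** The 95% half-width of a pairwise contrast in SD units is t(0.975, df) × √(2/n), with variance pooled over three arms. At n = 20 and df = 60 − 3 = 57 it is 0.633. The largest one-clinic pooled shift, 0.133, lies well inside this.

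**4. Cost of including centre.** Two more parameters leave df = 55, and residual variance is multiplied by 1 − r, where r is the assumed share of outcome variance explained by centre.
- r = 0: 0.634
- r = 0.1: 0.634 × √0.9 ≈ 0.601
- r = 0.2: 0.634 × √0.8 ≈ 0.567

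At worst the half-width grows by 0.001 SD. If centres differ in outcome level, it shrinks.

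**5. Precision within one centre.** With n = 20/3 and df = 20 − 3 = 17, the half-width is 1.156 SD. Even the extreme 0.8 SD gap between two centres could not be established from by-centre contrasts alone. They have to be read beside the logged exposure.

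**The case against.** The permission is deliberate and pragmatic. Cost bearers may require certain therapy, the add-on design is disclosed, and exposure must be recorded. With a list per centre, usual care should balance between arms within each centre, so nothing is confounded. No clinic is said to give either treatment routinely, and off-study CaCT or AP need not use the study's RehaCom modules or acupuncture points. Every magnitude above is assumed. All of this stands, and it is why the point is minor.

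Two objections concern the centre term. An article may leave model factors to a fuller plan, so the absence of centre is not in itself a fault. It is raised because the named tests are plain group comparisons beside centre-wise randomisation, and Kruskal-Wallis as named has no place for a centre factor. Also, a centre main effect or a stratified rank test still yields one pooled contrast and cannot by itself show that the contrast differs by centre. That is correct, and it is why by-centre reporting is needed as well.

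Three stronger readings are tempting but unsupported:
- **The comparison is biased or invalid.** It is not; it estimates the effect of assignment on top of the usual care actually given.
- **The protocol contradicts itself.** The RehaCom section says "it is better to use a computer-assisted training program to ensure patients from different centres will all receive equal treatments". That explains the choice of study training and makes no promise about usual care.
- **The follow-up trial will be mis-sized.** The Sample size section says "The results will be used to compute sample size and conduct a power calculation to plan the full-scale follow-up study". If the follow-up keeps the same usual care, the pilot estimate is the right input, and nothing in the document says usual care will change.

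**Conclusion.** The point holds as an optional, low-severity improvement. The protocol lets the arm-defining treatments enter usual care in any arm by clinic practice, without a stated cap, and the analysis it names uses neither the centre structure nor the log that would show whether this happened.

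The effect on the contrasts is unknown and may be zero. The illustrated attenuation (a factor of 1.00 to 0.67 for one clinic, 1.00 to 0.33 for two) and the between-centre gap (0 to 0.8 SD) rest on assumed exposure of all patients in a clinic, assumed redundancy and, for the gap, an assumed 0.4 SD per component. What does not depend on those assumptions is that including centre costs almost nothing in precision and that the exposure data are already to be collected.

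**What to change.** 1. Include centre as a factor in the ANOVA. In the non-normal branch, replace Kruskal-Wallis with a rank test stratified by centre. Cost: 2 degrees of freedom, and a half-width of 0.634 instead of 0.633 SD if centre explains nothing.
2. Report the arm contrasts by centre, descriptively, beside off-study CaCT and AP minutes by arm and centre taken from the log already required. Cost: one extra table and no new data. Downside: each centre has about 7 patients per arm and a half-width of about 1.2 SD, so these contrasts support no test or claim about any single centre.
3. Describe the estimate as the effect of assignment on top of usual care that may include CaCT or AP. Cost: wording only.

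Usual care needs no restriction, and no new data items are needed.
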